### The transition programme

The study in focus of the process evaluation reported here is the STEPSTONES project, which is a person-centred transition programme for adolescents (age 16–18.5 years) with CHD. The programme was developed from a brief transition intervention previously tested in Belgium.^19^ To adjust this intervention to the Swedish context, qualitative and quantitative preparatory studies were performed on the target population.^20–23^ Furthermore, stakeholder involvement, literature review and behavioural change theories were applied, following the protocol for developing health promoting programmes, intervention mapping.^24^ The programme aims to be generic, and thus applicable to other CCs. However, CHD was chosen as the target population of this intervention, being the most common congenital malformation in need of life-long follow-up.^25^ The programme consists of eight key components, implemented in five steps (see figure 1). A transition coordinator (TC) operating at each intervention centre delivers the programme. The TC is a specialised, paediatric nurse who has received tailored training in delivering the intervention.

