#### Participants and setting: RCT study

The STEPSTONES programme is evaluated through a hybrid RCT, where a longitudinal observational study is embedded within the RCT (figure 2). The study is performed in seven university hospitals in Sweden where two centres consist of an intervention group (n=70), and a comparison group (n=70) where individual randomisation is performed to either of the groups. The remaining five centres constitute additional control groups (n=70) where no contamination of the intervention is expected. The hypothesis is that adolescents randomised to receive the transition programme over a 2-year period will have a higher patient empowerment score compared with those randomised to usual care. Inclusion criteria for participants in the RCT study are: 16 years of age with CHD, Swedish speaking and literate. Their parents will also be invited to participate. The study is ongoing and will be concluded in 2021. A study protocol describing the RCT has been published.^26^ The process evaluation of the STEPSTONES project is conducted alongside the effectiveness evaluation and health economic evaluation in order to understand and explain the outcomes of the trial. Since the process evaluation is extensive, covering several different aspects of programme delivery, the full extent of this evaluation is reported in this paper.

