#### Quantitative data collection

The following data sources will be used to collect quantitative data on process measures:Enrolment formThe enrolment form is based on the five delivery steps of the intervention (see figure 1). The data allow for the measurement of adherence and attendance in the intervention for all eligible participants. Drop out from the study, non-attendance for visits and reasons for this will also be registered, which gives information about acceptability of the transition programme.
Intervention implementation formThis form will be filled out by the TC after each individual patient encounter, whether in person, by telephone, text message or email. This form contains the components of the intervention, for example, information and education about the health condition, treatment and health behaviour, and information about the adult care follow-up. It also gives information about topics covered, supportive activities and recommendations given, providing an indication about adherence, and dose delivered of the intervention to the patients. The data source will also give information on which communication channel is primarily used for contact between the TC and patients.
Adverse event (AE) reportThe occurrence of AEs will give an indication of potential attrition from the study.
Transition plansEach patient in the intervention receives a transition plan in which the care is documented. An analysis of this plan will be undertaken to understand what the main objectives were in the transition of individual patients. This analysis will estimate which components of the intervention have been delivered, the outcomes of these and how this is documented. The data from these sources will give information about the possible mechanism of impact, adherence, dose and the potential effects of moderating factors on fidelity such as patient characteristics.
Sociodemographic dataAge, sex, education level, diagnosis and pharmacotherapy, comorbidities, geographic location, living situation, country of birth, parental marital status and employment situation will be retrieved from the Swedish registry of CHD (Swedcon) and the questionnaires used in the RCT. These data will be used to examine the characteristics of participants who engage with and continue participation in the intervention, and those who do not (eg, drop outs and non-participants), and how this affects the reach of the programme.

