### Data analysis

#### Quantitative data analysis

The process variables (eg, adherence and dose) retrieved from the enrolment form, intervention implementation form and sociodemographic data will be entered into a database and analysed in the Statistical Package for the Social Sciences by using descriptive statistics with frequency distributions, proportions, variability over time and means. The effect on process variables of intervention centres’ characteristics and patients’ sociodemographic factors will be analysed by regression analysis, as will data from the time management form, to explain potential moderators on fidelity. The reach of the intervention (ie, did the intended population participate in the study) will be assessed by comparing participants versus non-participants of the RCT with sociodemographic data and clinical data (eg, disease characteristics). The MRC guidance recommends reporting results of the process evaluation separately from the effectiveness evaluation to avoid biased interpretation of effectiveness results.^17^ We are following this recommendation but will in addition perform a post-hoc regression analysis on dose–outcome relationships as well as subgroup analysis for relevant clinical and demographical variables.

The data from the transition plans will be analysed using descriptive statistics along with quantitative content analysis^39^ using the software NVivo (QSR International Pty V.12, 2018) by counting word occurrences related to the components of the intervention to summarise what the main objectives were of each individual participant’s transition. AEs will be analysed if they occur.

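### Counting component-related words in the transition plans cannot by itself show which components were delivered or with what outcome, which is part of what the plan analysis is meant to estimate

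*Protocol article*

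**What the plan says.** Two sections of the Protocol article deal with the transition plans.

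- **Quantitative data collection, Transition plans.** The first purpose is each patient's goals: "An analysis of this plan will be undertaken to understand what the main objectives were in the transition of individual patients". A second purpose follows at once: "This analysis will estimate which components of the intervention have been delivered, the outcomes of these and how this is documented". The entry closes by saying that data from these sources, in the plural, will inform mechanism of impact, adherence, dose and moderators of fidelity.
- **Quantitative data analysis.** "The data from the transition plans will be analysed using descriptive statistics along with quantitative content analysis", done in NVivo "by counting word occurrences related to the components of the intervention to summarise what the main objectives were of each individual participant’s transition". No other step is described for this source. Adherence and dose are taken up in the preceding paragraph of that section, which draws on the enrolment form, the implementation form and the sociodemographic data and does not mention the plans.

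On the programme itself, the section The transition programme states: "The programme consists of eight key components, implemented in five steps". The intervention group numbers 70, and each of these patients is to receive a plan.

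**The concern.** The stated purpose and the stated method do not match. The purpose covers delivery of components and their outcomes. The only concrete operation described is a word count, and the only use given for it is to summarise objectives. A reader who carried out the analysis as described would finish with frequencies of component words and no measure of what was delivered or achieved.

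The risk lies in interpretation. If the counts are reported under the purpose set in the data collection section, a component that is often mentioned may be taken as one that was well delivered, and a long plan as a high dose. The plans are also meant to be cross-checked against other sources. For that, the plans must yield a measure of delivery comparable with what the implementation form records, and a word frequency is not one.

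**Working it through.** The article gives no figure to reproduce. The check sets purpose against method and then looks at how a count behaves.

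**1. Purposes against method**

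| Purpose set under Quantitative data collection | Served by the word count under Quantitative data analysis? |
|---|---|
| Main objectives of each patient | Yes, this is the stated use, though the most frequent word need not be the main goal |
| Which components were delivered | No; a mention is not a delivery |
| Outcomes of those components | No; a goal set and a goal met can contain the same words |
| How this is documented | In part; presence or absence of component words shows what was written about |

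Two of the four purposes have no matching method.

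**2. What a count can distinguish.** For one component in one plan, four states matter: planned, delivered, declined, achieved. The component's words can appear in all four. A positive count is compatible with any of them, and so is a larger count.

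**3. Effect of plan length.** Let w_j be the count for component j in a plan. Suppose another plan describes the same delivered components at k times the length throughout.

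- Each raw count becomes k × w_j. The value of k is an assumption, since the article says nothing about plan length. For k from 1 to 3, raw counts differ 1- to 3-fold with identical delivery.
- The share of component j within the plan is (k × w_j) / (k × Σw) = w_j / Σw, which is unchanged.

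Uniform wordiness therefore leaves the ranking of components within a plan as it was, and the use for individual objectives survives. Comparisons of raw counts between plans, or between groups of plans, do not.

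**4. Size of the alternative.** Three yes/no items for each of eight components is 3 × 8 = 24 entries per plan. For at most 70 plans this is 24 × 70 = 1,680 entries.

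**The case against.** The strongest case on the other side has four parts.

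- **The count is asked to do less than this suggests.** It is tied to objectives within each individual plan, where uniform verbosity does no harm. This stands for the objectives purpose. It does not supply a method for delivery and outcomes.
- **The named method is broader than a count.** Descriptive statistics and quantitative content analysis could include coding, and a journal article may leave the dictionary, the handling of negation and any length adjustment to a fuller plan. Leaving out such detail is no fault. However, the sentence itself specifies the content analysis as word counting, so the broader label does not close the gap.
- **Delivery is measured elsewhere.** The implementation form is completed after each encounter, visits are observed with a structured protocol that includes components from that form, and participants are interviewed about dose received. The Discussion also calls for quality control and cross-checking between sources. This stands, and it limits the consequence.
- **The count is not worthless.** It is restricted to component-related words, so it is a crude indicator of which components were documented. This also stands.

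A reader might infer more: that the counts will produce a false difference in fidelity between centres, because each centre has its own coordinator and writing style cannot be separated from centre. The article does not support this as a finding. It plans no test or regression of plan word counts by centre; the regression on centre characteristics concerns other sources. That there are two coordinators is itself inferred, from "A transition coordinator (TC) operating at each intervention centre delivers the programme" together with "two centres consist of an intervention group (n=70", and the article does not say who writes the plans. Nor does it treat the plans as independent of the coordinators' other records. It names reliance on the coordinators as a limitation and adds data from participants and healthcare professionals.

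**Conclusion.** The point holds in a limited form. The analysis of the transition plans is meant to estimate which components were delivered and their outcomes, and the word count described for it cannot do so alone. It can support a summary of documented objectives. Raw counts should not be used as a measure of delivery or set side by side across centres.

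The gap affects one supplementary source of at most 70 plans. It does not touch the trial's primary outcome, and the other sources on delivery remain. The conclusion rests on the article's own description of purpose and method. The remark on plan length assumes only that plans differ in length. No rate of false findings is attached, because that would require a comparison the article does not plan and plan lengths it does not give.

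**What to change.** In Quantitative data analysis, replace the count as the main measure with a fixed coding of each plan. For each of the eight components, record yes or no for objective recorded, delivered, and outcome documented. Report each as a proportion of the plans, stating how many of the 70 patients have one. Cross-tabulate the delivered item with the implementation form, component by component. Use the NVivo word search only to locate the relevant text.

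If this is not wanted, narrow the purpose in Quantitative data collection to objectives and documentation, and leave delivery to the implementation form and the observations.

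The coding would take some days, with data and software already in place; narrowing the purpose costs one sentence. The checklist codes the same documents, so it does not remove dependence on whoever wrote them. The cross-tabulation shows only where plan and form agree or disagree.

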#### Qualitative data analysis

Design, sampling, analysis and reporting of the qualitative findings will follow the Consolidated Criteria for Reporting Qualitative research.^40^ Qualitative data will be analysed with manifest content analysis, as described by Graneheim and Lundman.^41^ The MRC guidance for process evaluation will act as a coding matrix for the qualitative data in the analysis phase.^17^ All qualitative data analysis will be performed in the software NVivo.

### Integrating quantitative and qualitative data

Analysis and reporting of the mixed-method study will follow the Good Reporting of A Mixed Methods Study framework.^42^ The mix of quantitative and qualitative data can give information about contextual factors that affect implementation and potential moderating factors on fidelity.^17^ Qualitative data can be used to explain quantitative findings.^33^ The integration of data will be performed by creating a triangulation protocol, which works as a scheme where the different data sources are combined and findings from different components of the process evaluation are listed and compared. By looking for agreement and disagreement between the data sources, the findings may lead to a better understanding of the results.^43^

### Patient and public involvement

The STEPSTONES project was developed with the support of an advisory board and panel of international experts consisting of stakeholders, that is, young adults with CHD, parents, clinicians, researchers and representatives from the patient organisation. Patients will not be involved in the recruitment of this study; however, young adults with CHD will be involved during the adolescent day sharing their experiences of the transfer to adult care and transition to adulthood, acting as role models and providing peer support. Dissemination of results to study participants will be delivered through the patient organisation and social media.

### Ethics and dissemination

Adolescents, parents and healthcare professionals in the RCT have consented to participation after receiving written and oral information about the study. Written consent to participate in the qualitative data collection will be requested after additional written and oral information about the study. Ethical approval for the study was received from the Regional Ethical Review Board in Gothenburg, Sweden (No. 931-15), and the study will be performed in accordance to the Declaration of Helsinki.^44^ Findings of the process evaluation study will be published in open access, peer-reviewed scientific journals and presented at national and international conferences.

## Discussion

Process evaluation studies have been increasing in recent years and are imperative to explaining how complex interventions produce the desired outcomes. Furthermore, such evaluation studies are arguably more important when interventions fail to produce the intended outcomes. Since its release in 2015, MRC guidance has been used in process evaluation studies, providing extensive data on important aspects of interventions delivery.^45 46^ However, MRC does lack certain potentially important aspects, for example, the impact of recruitment and the internal and external validity of the RCT on outcomes. For this reason, we have added these research questions to our protocol.

The proposed study has several strengths. First, solid funding of the process evaluation has allowed us to employ adequate number of research staff to handle logistics regarding recruitment, data collection and analysis. Furthermore, the documentation of process variables is digital and can be followed up continuously from the main research site.

Second, when implementing a complex intervention, a clear description of the intervention is beneficial, as a benchmark for evaluators and for those delivering the intervention. Previous studies show that complex interventions with clear descriptions have a greater chance of being implemented with high adherence.^47^ The logic model of our intervention was developed using the framework of intervention mapping, which provides a thorough evidence base.^24^ In addition, the materials, resources and training for the TCs can facilitate delivery, enhancing intervention fidelity.^30^ This process evaluation study can thus add to the existing evidence on how frameworks, such as intervention mapping, can aid in intervention development and evaluation.^24^

Third, the planned extent of data sources, methods and scope of data collection have, to the best of our knowledge, not been applied in previous process evaluation studies. This is beneficial for many reasons. The use of various sources can strengthen understanding of how different factors interact in creating outcomes. A recent review concluded that only one quarter of all studies measuring fidelity and engagement in interventions used multiple data collection methods such as observations and self-reported measures.^48^ A range of qualitative methods within intervention studies can therefore strengthen the evaluation since these methods are forceful in capturing contextual factors.^32 49^ Moreover, quantitative data provide measures for important process variables such as fidelity.^30^ By collecting data throughout the trial, this study can also handle the impact of ‘teething problems’ (eg, TCs learning curves) by following changes over time and combining quantitative measures with stakeholder interviews.^17^

Finally, the findings of the process evaluation will be reported separately from the effectiveness evaluation, avoiding biased interpretations of results and therefore strengthening the validity of the findings.^17^ Since the process measures in this study rely on routine monitoring data, validity of these documents has to be ensured by quality control and cross checking between different sources. Routine monitoring data are effective in reducing response bias; they are cost effective and allow for analysis over time.^17^

However, some challenges and limitations of this process evaluation study have to be considered. Factors affecting recruitment are not directly included in the qualitative data collection. In Steckler and Linnan’s^50^ framework, this is a part of the process evaluation which is not included in the MRC guidance.^17^ Recruitment pace, selection of study participants and recruiters’ skills could arguably be considered moderating factors on reach and outcomes. Moreover, the considerable amount of questionnaires distributed to participants in the effectiveness evaluation might affect willingness to participate and therefore adherence. That said, the acceptability of the intervention is explored and measured, and so is reach in terms of participants approached and recruited. Furthermore, the TCs performing the intervention, and their performance during the intervention, will have a great impact on many of the key process measures since they are the only personnel delivering the intervention. To manage this, data will also be collected from participants and healthcare professionals in order to broaden the perspective. Process evaluators should also be aware of how they impact the quality of the collected data (eg, Hawthorne effects), especially in participatory observations.^51^ However, a small subsample of qualitative observations from a total of 210 outpatient visits should arguably give little or no impact on effectiveness outcomes of the RCT. Nevertheless, it may affect the quality of the process evaluation results. To manage this, establishing good relations between the researchers performing the process evaluation and the TCs and healthcare professionals is important to get access to the field and retrieve trustworthy data. Informal interviews in connection with observations can also strengthen trustworthiness.^49^

## Conclusions

Transfer of care for adolescents living with CCs is a timely issue, and the effectiveness and causal assumptions of transition programmes are yet to be proven. It is therefore imperative to conduct high-quality process evaluation studies to understand how the programmes are delivered, for whom they are delivered and under what circumstances. The effect of contextual factors and possible moderating factors on intervention fidelity and participant engagement may also increase transferability of findings and can thus inform the implementation of transition programmes in other settings.
